#### Randomization

The study will be individually randomized. The randomization and patient allocation will be fully centralized. A central randomization service provided by the University of Turku will be used. Allocation will be computer generated. The participants will be randomly assigned (a block randomization in three blocks) using numbers via computerized assignment developed by the independent trial statistician and implemented by the Research Assistants (2), who are trained in patient randomization and data collection.

The research assistants overseeing patient recruitment and randomization will be aware of the assignments. Allocation will not be masked to participants in intervention and control groups or Research Assistants who will recruit patients. The psychologists, as cognitive outcome assessors, will be masked. The data analyst (the trial statistician) will be kept blinded to the allocation. As far as we are aware, there will be no contact between participants in different groups; participants will come from a wide geographic area in the catchment area of the Southwest Hospital District in Finland.

#### Analysis Plan

All the participants will be analyzed at the baseline, after 8 weeks when the intervention has been finalized, and at 3 months, using all the scales for primary and secondary outcomes. Comparisons in possible differences between means in 3 intervention groups and 3 time points will be conducted using analysis of variance (ANOVA test). Possible post hoc tests may be performed using paired *t*-tests, or Chi square tests to detect significant differences before and after treatment in sub-groups, if needed. Further, significant differences between groups will be evaluated applying the unpaired Student’s *t*-test using the conventional 95% level of confidence. Statistical analyses will be done using SAS System for Windows, version 9.4 (SAS Institute Inc.). *P* values less than 0.05 will be considered statistically significant.

The cumulative monitoring data during the 8-week period regarding gaming for the total number of received parameters (frequency, timing, time) will be calculated. Feasibility information (secondary outcomes) available for each patient will be calculated (participation/refusal rate, measurement instrument filled, drop-outs, acceptability, usability, satisfaction, willingness) and compared to the highest possible representative numbers (100% participation rate; measurement instrument filled, drop-out rate 0%, acceptability 100%, usability 100%, satisfaction 100%, willingness to use games in the future 100%).

Criteria for feasibility are as follows:

Willingness to participate 80% (refusal rate 20%)We expect that more than 75% of the prescheduled measurements will be performed (adherence).Less than 25% of participants drop out for to any reason (adherence)The acceptability of the game use is at least 95% (in intervention and control groups) (adherence).Usability evaluation for the gaming system is at least 80% (1 item; dichotomous scale yes/no) (usability).More than 80% are satisfied with the games (1 item; dichotomous scale, yes/no) (satisfaction)We expect that 60% are willing to use the games later as part of their recovery process (use in the future).

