#### Primary Outcome

##### Processing Speed and Visuomotor Tasks

*The Trail Making Test (TMT)* requires visual search, scanning, speed of processing, mental flexibility, and executive functions [39]. The test consists of two parts. In the first part, patients are given a paper displaying circles numbered 1 to 5 in random order. The patient is told to draw lines that will connect the numbers in ascending order. In the second part, there are circles with numbers from 1 to 13 and letters from A to L. This time, the patient draws lines to connect the circles so that they alter between numbers and letters in an ascending order (for example: 1-A-2-B-3-C) and so on. The time it takes to complete the trail is measured in both parts of the test. Errors do not affect the final score, but they must be corrected by the patient [40,41].
*WAIS-IV tasks* (symbol search, coding and cancellation*)* are a test package used to measure cognitive skills of adult patients, especially skills of sorting out simple visual information, monitoring, making progress in the task, maintaining attention, visuomotor co-ordination and visual memory [42]. The tasks constitute 4 indices that measure different areas of cognitive skills. In symbol search and cancellation tasks, the participants perform a visual search in order to find out if a certain symbol is in the midst of other symbols. In the symbol search task, the symbols are organized in rows, and the participant has to indicate whether or not the required symbol was on each row. In the cancellation task, the participant looks for the same symbols during the whole task. In the coding task, the participant is given a set of numbers and symbols that match each other. Their task is to fill out an empty grid containing only numbers with the appropriate symbols matching those numbers. The test-retest reliabilities of the tasks used in this study ranged from 0.78 to 0.86 over an 8-82 day period in the original WAIS-IV standardization study [42]. A version of the test [42] containing norms for the Finnish population is used in this study.

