#### Time for the Data Collection and Follow-Up

Patient data will be collected at three different times: at baseline, after the intervention (8 weeks), and as a follow-up, 3 months after the intervention. If required by the participant, he or she will receive a text message about 2 days before the meeting to remind them of the coming follow-up meeting.

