#### Sample Size

The calculations for the sample size needed in each group are preliminary estimations to guide our data collection, which are based on previous studies: (1) TMT (version A) and (2) depression (PHQ-9). First, if a score on the TMT version will be about 71, the mean change in the scores during the follow-up will be 30, and standard deviation of the TMT scores will be 53 [41]. This difference between groups could be expected to be significant (with a power of 85%, *p*=.05) if the sample size in each group is 30 subjects. Second, if the average level of the PHQ-9 score is about 10, the mean change in the scores during the follow-up is then 3 (SD 5) [48]. The difference could be expected to be significant (with a power of 85%, *p*=.05) if the sample size in each group is 27 subjects. Thus, based on these preliminary power calculations, the sample size to be used in this study (30 in each group) is not very strong but will be reasonable for a feasibility study aiming to detect preliminary changes within the group, between baseline and follow-up outcome measurements. However, this means that the attrition rate of the study should be near 0%. The outcomes of this study will be used as a guide to estimate a sample size for a multi-center study to be conducted, hopefully in the future.

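### No between-arm comparison is stated to adjust for baseline, and the ANOVA and unpaired t-test are worded too loosely to show how far baseline is used

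*Protocol article*

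**What the plan says.** The Analysis Plan section of the protocol article names the efficacy tests. The first is an ANOVA: "Comparisons in possible differences between means in 3 intervention groups and 3 time points will be conducted using analysis of variance (ANOVA test"). Paired t-tests or chi-square tests may follow, "to detect significant differences before and after treatment in sub-groups, if needed". For the arms it then says that "significant differences between groups will be evaluated applying the unpaired" Student's t-test, and that P "values less than 0.05 will be considered statistically significant".

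Data are collected "at baseline, after the intervention (8 weeks), and as a follow-up, 3 months after the intervention", so baseline is one of the ANOVA's three time points. The Interventions section puts the questionnaires and cognitive tests before allocation.

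The article does not say whether the ANOVA has a within-person term, which of its effects is the test of treatment, or whether the t-test uses follow-up or change scores. The only covariate control it mentions is for the amount of gaming recorded in the diary (Interventions).

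Two other statements bear on the size of the issue. For the WAIS-IV primary tasks, "The test-retest reliabilities of the tasks used in this study ranged from 0.78 to 0.86", over 8 to 82 days. For the Trail Making Test, the Sample Size section assumes a score of about 71, a mean change of 30, and that the "standard deviation of the TMT scores will be 53".

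**The concern.** Each participant's pre-randomisation score is already in hand and, for the WAIS-IV tasks, strongly predicts the later score. Using it as a covariate is the cheapest precision available to a trial of 30 per arm. The plan does not say that it will do so.

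The wording also admits analyses that behave very differently on the same data: a t-test that leaves baseline out, a repeated-measures interaction that uses it well, or a factorial ANOVA that counts one person's three visits as three people. In every form of the ANOVA, the group main effect averages in a baseline visit at which no treatment effect can exist. At stake are the chance of seeing the planned difference between arms, and the value of the estimates as a guide to the later multi-centre study.

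**Working it through.** **Inputs.** TMT-A change 30, SD 53; PHQ-9 change 3, SD 5; 85% power; 30 and 27 per group (Sample Size). Alpha 0.05 (Analysis Plan), taken as two-sided because the article does not say. Correlation r = 0.78 to 0.86 from the WAIS-IV reliabilities (Primary Outcome). No correlation is given for TMT, PHQ-9 or TBI patients, so r = 0.5 and r = 0.3 are added as assumptions.

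**Reproducing the plan's figures.** The one-sample (paired) t formula at 30/53 = 0.566 gives n = 30.0, and at 3/5 = 0.6 gives n = 26.9. These match 30 and 27. The two-sample t formula needs about 57 and 51 per arm. The stated numbers therefore treat 53 and 5 as SDs of change within a group, although the text calls 53 the SD of the scores.

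**Variances, relative to a t-test on follow-up scores (= 1).**
- Change from baseline, which is what a repeated-measures group-by-time contrast compares: 2(1 − r).
- ANCOVA: 1 − r².
- Efficiency of change against ANCOVA: (1 − r²)/[2(1 − r)] = (1 + r)/2.

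**Power, 53 read as a cross-sectional SD.** Difference 0.566 SD, 30 per arm, noncentral t; the standardised effect is 0.566 divided by the square root of the relative variance.

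| r | Variance of follow-up t-test ÷ ANCOVA, 1/(1 − r²) | Power, follow-up t-test | Power, change contrast | Power, ANCOVA | Loss of change against ANCOVA |
|---|---|---|---|---|---|
| 0.30 (assumed) | 1.1 | 58% | 45% | 62% | 35% |
| 0.50 (assumed) | 1.3 | 58% | 58% | 70% | 25% |
| 0.78 | 2.6 | 58% | 90% | 93% | 11% |
| 0.86 | 3.8 | 58% | 98% | 99% | 7% |

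A follow-up t-test throws away r² of the attainable information: 61% at 0.78 and 74% at 0.86, but 25% at 0.5 and 9% at 0.3. It exceeds half only when r is above about 0.71.

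**Power, 53 read as an SD of change.** The 58% then belongs to a t-test on change scores. The ANCOVA SD is 53 × √[(1 + r)/2], so the effect becomes 0.566/√0.89 = 0.600 at r = 0.78 and 0.566/√0.93 = 0.587 at r = 0.86. Power is about 63% and 61%.

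**The ANOVA with visits treated as independent.** The variance of an arm's average over three visits is understated by a factor 1 + 2r. With 2 and 261 degrees of freedom the 5% critical value is about 3.03, and the true rejection rate under no effect is about exp[−3.03/(1 + 2r)]:
- r = 0.5: exp(−3.03/2.00) = 22%
- r = 0.78: exp(−3.03/2.56) = 31%
- r = 0.86: exp(−3.03/2.72) = 33%

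Simulation (3 arms of 30, 3 visits, equal correlation) gives 22–23%, 30–31% and 33%. The group-by-time test in that model almost never rejects under no effect, and has only 2% to 4% power at 0.566 SD for r = 0.78 to 0.86.

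**The ANOVA fitted as repeated measures.** In the same simulation the group-by-time test keeps its size at about 5%. The group main effect also keeps its size but is diluted: an effect present at two of three visits averages to two thirds, 0.566 × 2/3 = 0.377 SD.

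**The case against.** The strongest reply is that the lead analysis does use baseline. An ANOVA over three groups and three time points is ordinarily fitted as repeated measures, and its interaction compares changes. Against ANCOVA that costs 7% to 11% at the WAIS-IV reliabilities. This stands. A reader might infer that the plan as a whole discards most of its precision, but the documents support that only for an unpaired t-test on follow-up scores, and only if r exceeds about 0.71. The Sample Size section speaks of mean change, so the t-test may equally be meant for change scores.

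A reader might also infer that the trial will run at a type I error of 22% to 33%. That requires treating visits as independent. The text does not say so; it only omits to name the within-person structure, and a condensed article may do that. The figure shows the outer edge of what the wording permits, not what is planned.

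The rise from 58% to 93–99% combines a TMT effect with WAIS-IV reliabilities from a standardisation study. The 8-to-82-day interval covers the 8-week visit but not a visit three months after an 8-week intervention. It also depends on 53 being a cross-sectional SD, whereas the stated sample size reproduces only if 53 is an SD of change. All of this stands and is why the range is shown.

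Finally, this is a feasibility study, and an unadjusted comparison of randomised arms is unbiased. That lowers the severity. It does not remove the point, because the article does state its between-arm tests and a better one costs only wording.

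**Conclusion.** The point holds in a limited form. No between-arm comparison is stated to adjust for baseline, and both the ANOVA's within-person structure and the score used in the t-test are left open. The size depends on the reading:

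- **Unpaired t-test on follow-up scores:** 2.6 to 3.8 times the ANCOVA variance at r = 0.78 to 0.86, 1.3 times at r = 0.5, 1.1 times at r = 0.3.
- **Repeated-measures group-by-time test:** a modest loss of 7% to 11% at r = 0.78 to 0.86, and 25% at r = 0.5.
- **Power at the TMT planning values:** adjustment lifts 58% to 93–99% only if 53 is a cross-sectional SD and TMT correlates over time as the WAIS-IV tasks do. If 53 is an SD of change, the gain is a few percentage points.

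The group main effect should not serve as the treatment test under any reading. These figures assume two-sided 0.05, 30 analysed per arm and equal variances. Severity: should-fix.

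**What to change.** Name one linear mixed model per outcome as the between-arm analysis, in place of the unpaired t-tests:

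- Response: the 8-week score and the score three months after the intervention.
- Fixed effects: arm, visit, arm-by-visit, and baseline score with a separate slope at each visit.
- Unstructured within-person covariance.
- All randomised participants with at least one follow-up score.
- Report the arm contrasts at each visit with 95% confidence intervals.

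If the three-by-three ANOVA is kept as a description, state that it is repeated measures and that the group-by-time term, not the group main effect, addresses treatment.

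As an optional secondary step, analyse TMT times on the log scale with log baseline. A mean of 71 with an SD of 53 implies right skew: a normal distribution would put about 9% of times below zero. The drawback is that effects become ratios, and any power gain depends on an assumed lognormal shape.

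The cost is analysis wording only. The SAS version already named can fit the model, and no new data are needed. Participants who miss one follow-up visit still contribute, which helps because the feasibility criteria accept dropout of up to 25%.

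### The trial is sized for within-group change and optional before-after tests are allowed at p<0.05, but a within-arm result cannot separate a game effect from practice

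*Protocol article*

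**What the plan says.** All references are to the protocol article.

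- **Sample Size.** For TMT version A the inputs are a mean change of 30 and a score SD of 53, giving 30 per group. For PHQ-9 they are a mean change of 3 with SD 5, giving 27 per group. Both claim 85% power at p=.05. The TMT calculation is presented as a contrast between the groups, but the section then concludes that 30 per group is reasonable for a "feasibility study aiming to detect preliminary changes within the group, between baseline and follow-up outcome measurements". It adds that the outcomes will inform the size of a later multi-centre study.
- **Analysis Plan, main analysis.** "Comparisons in possible differences between means in 3 intervention groups and 3 time points will be conducted using analysis of variance (ANOVA test"). In addition, "significant differences between groups will be evaluated applying the unpaired Student’s" t-test.
- **Analysis Plan, follow-up tests.** The before-after t-tests are conditional: "Possible post hoc tests may be performed using paired". The alternative that the section names is "Chi square tests to detect significant differences before and after treatment in sub-groups, if needed". One threshold serves everything: P "values less than 0.05 will be considered statistically significant".
- **Time for the Data Collection and Follow-Up.** "Patient data will be collected at three different times": baseline, 8 weeks, and 3 months after the intervention.
- **Primary Outcome.** The measures are TMT completion time and three WAIS-IV tasks (symbol search, coding, cancellation). The retest reliabilities given for the WAIS-IV tasks are 0.78 to 0.86 over 8 to 82 days.
- **Interventions.** One of the three arms is a passive control without gaming organized by the project.

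**The concern.** The objective is the effect of the games on cognition. When the same timed tests are sat three times, any gain from repeating them becomes part of the before-after change in every arm. The passive arm is there to subtract that gain, but a paired test inside a gaming arm makes no use of it.

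The Sample Size section names within-group change as what the trial should detect, while describing one of its two calculations as a between-group contrast. The Analysis Plan allows before-after tests at the same 0.05 threshold as the between-group tests and does not say which result carries the conclusion about the games.

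Two things are at stake. A significant within-arm change could be taken for a game effect when there is none. And if such a change were used to size the multi-centre study, it would include practice, so the assumed effect would be too large and the study too small.

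**Working it through.** **1. Reproducing the stated sizes.** Two-sided alpha of 0.05 is assumed, because the article does not state sidedness.

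*Paired test within one group.* Standardized change d = change/SD; noncentrality d√n; n−1 degrees of freedom.
- TMT-A: d = 30/53 = 0.566. At n = 30 the noncentrality is 0.566 × 5.477 = 3.10 and power is 84.99% (31 for a strict 85%).
- PHQ-9: d = 3/5 = 0.6. At n = 27 the noncentrality is 0.6 × 5.196 = 3.12 and power is 85.1%.

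*Comparison of two arms.* Normal formula: n per arm = 2(1.960 + 1.036)²/d².
- TMT-A: 2 × 8.98/0.320 = 56.0, so 57 (58 by the t distribution).
- PHQ-9: 2 × 8.98/0.36 = 49.9, so 50 (51 by the t distribution).
- One-sided versions need 45–46 and 40–41.

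Only the two-sided paired test returns 30 and 27. For TMT-A this reading uses the SD of the scores as the SD of the change, which is exact only at a baseline-to-follow-up correlation of 0.5, since √(2(1−0.5)) = 1.

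**2. Between-arm power on the same inputs, unadjusted.**
- TMT-A, 30 per arm: 57.8% (t) or 59.2% (normal).
- PHQ-9, 27 per arm: 58.1% (t) or 59.7% (normal).

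These figures treat the whole stated change as the difference between arms, that is, no change in the comparator.

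**3. A within-arm test when the games do nothing.** The SD of the change, in units of the score SD, is √(2(1−r)): 0.663 at r = 0.78, 0.529 at r = 0.86, and 1.000 at an assumed r = 0.5. With n = 30, significance needs an observed mean gain of 2.045/√30 = 0.373 SDs of the change. In score SDs that is 0.25, 0.20 and 0.37 respectively.

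Example: for a true practice gain of 0.2 SD and r = 0.78, d = 0.2/0.663 = 0.302, the noncentrality is 0.302 × 5.477 = 1.65, and the chance of p<0.05 is 36%.

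| Assumed practice gain | r = 0.5 (assumed) | r = 0.78 | r = 0.86 |
|---|---|---|---|
| 0.1 SD | 8% | 13% | 17% |
| 0.2 SD | 19% | 36% | 52% |
| 0.3 SD | 36% | 67% | 85% |
| 0.4 SD | 56% | 89% | 98% |

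**4. The same situation seen between arms.** Two arms of 30 were simulated with equal practice gain and r = 0.82 (20,000 runs).

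| Assumed gain, both arms | Within-arm test p<0.05 | Between-arm test of change p<0.05 | One arm significant, the other not |
|---|---|---|---|
| 0.2 SD | 43% | 5.2% | 49% |
| 0.3 SD | 75% | 4.9% | 37% |

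The between-arm test keeps its 5% level. A pattern of significance in one arm but not the other is common even though the arms do not differ.

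**The case against.** The strongest reply is that the plan already contains the right analyses. The ANOVA over groups and times comes first and the unpaired between-group tests are stated outright; both use the passive arm. The before-after tests are post hoc and conditional, and the sub-groups they apply to are not defined as the arms. Paired follow-up of a group-by-time ANOVA is common practice. This stands, and it limits the point: the within-arm tests are not the planned main inference. It does not remove the point, because the Sample Size section still names within-group change as the aim and its numbers support only that.

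The size of the practice gain is also open. The article gives none, and the reliabilities are WAIS-IV standardization values, not values for TMT or for people with brain injury. The 8-week visit (56 days) lies within the 8–82 day window; the last visit does not. This stands too, which is why the results are shown as a range.

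Several stronger readings are tempting and are not supported:
- *Practice would make the tests significant.* The chance runs from 8% to 98% over the assumptions shown, so only *could* is justified.
- *Natural recovery also drives the change.* Participants are more than 12 months past discharge from neurologic treatment, which weakens this.
- *Regression to the mean also drives it.* Nobody is selected for poor scores. Excluding people with evident severe impairment at baseline testing would, if anything, push the other way.
- *The chi-square test is invalid for paired data.* The article does not say which chi-square test is meant, and it defines no yes/no outcome with a baseline value; the yes/no items are feasibility items.
- *The within-arm result will be reported as the effect, or carried forward.* The article says neither; it only leaves room for both.

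The practice argument concerns the timed cognitive tests, not questionnaires such as PHQ-9.

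**Conclusion.** The point holds in a limited form. The Sample Size section contradicts itself on the contrast: 30 and 27 per group give 85% power for a paired within-group test and about 58% for an unadjusted comparison of two arms on the same inputs. That result needs only the article's figures and a two-sided test.

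The optional before-after tests cannot show a game effect on the timed tests. In an arm of 30 with no game effect they would be significant in 13–17%, 36–52% or 67–85% of cases for assumed practice gains of 0.1, 0.2 or 0.3 SD at r = 0.78–0.86, and in 8%, 19% or 36% at an assumed r of 0.5. The gains, the value 0.5, and the use of WAIS-IV reliabilities to stand for the speed tests generally are assumptions. This should be corrected, but it does not undermine the planned between-group analyses.

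**What to change.** 1. In the Analysis Plan, state that conclusions about the games, and the effect size carried to the multi-centre study, rest on between-arm contrasts: group-by-time, or follow-up score adjusted for baseline.
2. Report within-arm changes as means with 95% confidence intervals, without significance tests.
3. In Sample Size, reconcile the two descriptions of the contrast. Say that 85% power applies to a paired within-group test, and that an unadjusted between-arm comparison on the same inputs has about 58% power (TMT-A at 30 per arm, PHQ-9 at 27 per arm). Baseline adjustment can raise this; how far depends on the correlation in this population.

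The change is to wording only and needs no further participants or data. Its price is fewer p-values to report and a less favourable stated power, which is still compatible with a feasibility aim.

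### The Analysis Plan specifies no baseline-adjusted comparison between arms: its unpaired t-test has no baseline term, and its 3-by-3 ANOVA names no contrast

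*Protocol article*

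**What the plan says.** The Analysis Plan names two procedures for comparing arms.

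- The first is an ANOVA: "Comparisons in possible differences between means in 3 intervention groups and 3 time points will be conducted using analysis of variance". The section on time for data collection fixes the visits: "Patient data will be collected at three different times: at baseline, after the intervention (8 weeks), and as a follow-up, 3 months after the intervention". Baseline is therefore one of the three time points. The text does not say whether the model is repeated-measures, or whether the group main effect or the group-by-time term is the contrast of interest.
- The second is pairwise: "significant differences between groups will be evaluated applying the unpaired" Student's t-test. The variable analysed (follow-up score or change) is not stated.

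A participant's own scores are explicitly paired only in the optional paired t-tests, which are there "to detect significant differences before and after treatment in sub-groups, if needed". Those tests do not compare arms.

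No baseline covariate is named. The one statistical control that the article mentions, in the Interventions section, is for the amount of gaming. The same section places the baseline cognitive testing before allocation, so those scores are available as true pre-randomisation covariates.

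**The concern.** With 30 adults per arm, aged 18 to 65 and with mixed brain injuries, stable differences between people are likely to make up much of the spread in follow-up scores. A test that ignores the baseline score leaves that spread in its error term. It also lets whatever chance difference the arms had at baseline carry through to the follow-up difference. The article itself calls the sample not very strong and intends the results to guide a multi-center sample size, so imprecise estimates would carry forward. Adjusting for baseline addresses both problems with data already being collected.

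**Working it through.** **Inputs.** From Sample Size: TMT-A difference 30, SD 53 (30/53 = 0.566 SD), 30 per arm. From Analysis Plan: "values less than 0.05 will be considered statistically significant"; two-sided is assumed. From the Primary Outcome section, for the WAIS-IV tasks only: "The test-retest reliabilities of the tasks used in this study ranged from 0.78 to 0.86 over an 8-82 day period". No correlation r between baseline and follow-up is given for TMT or PHQ-9, so r = 0.3 and 0.5 are shown as assumptions. Equal SDs at all visits and no dropout are also assumed.

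**The plan's own figure.** For TMT the article says "This difference between groups could be expected to be significant (with a power of 85"%) with 30 per group. That n reproduces as a two-sided one-sample or paired t-test on change within one group: n = 30.0, power 0.850. The PHQ-9 figure does likewise (3/5, n = 26.9, stated as 27). As an unadjusted comparison of two arms, 85% power would need 57 and 50 per arm by the normal approximation. The planned n therefore gives no assurance about the between-arm test considered here.

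**Between-arm power.** The noncentrality is (30/53) × √(30/2) ÷ √f = 2.192/√f. Here f is the error variance relative to an unadjusted follow-up score: f = 1 for the raw score, 1 − r² for ANCOVA and 2(1 − r) for change scores. Degrees of freedom are 58, or 57 for ANCOVA.

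| r | f, ANCOVA | Power, ANCOVA | f, change | Power, change | Power, raw follow-up |
|---|---|---|---|---|---|
| 0.3 | 0.91 | 62% | 1.40 | 45% | 58% |
| 0.5 | 0.75 | 70% | 1.00 | 58% | 58% |
| 0.78 | 0.39 | 93% | 0.44 | 90% | 58% |
| 0.86 | 0.26 | 99% | 0.28 | 98% | 58% |

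The normal approximation gives nearly the same: 59% for the raw score, 94% and 99% for ANCOVA at the two WAIS-IV values, and 91% and 98.5% for change.

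**Interval width.** The 95% half-width is t × 53 × √(2/30) × √f. It is 27.4 points unadjusted. With ANCOVA it is 23.7, 17.1 and 14.0 points at r = 0.5, 0.78 and 0.86.

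**ANCOVA against change scores.** The variance ratio is (1 − r²)/(2(1 − r)) = (1 + r)/2. This is 0.89 at r = 0.78 and 0.93 at r = 0.86, so change scores give up 11% and 7% of variance there. At r = 0.5 the change score has f = 1, no gain over the raw score; below 0.5 it is worse than the raw score.

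**The ANOVA under two readings.**

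- *Group main effect over three visits.* With an equal effect at both follow-ups and none at baseline, the effect becomes 2/3 × 0.566 = 0.377 SD. The variance of a person's mean is (1 + 2r)/3. For two arms, power is 42%, 34% and 33% at r = 0.5, 0.78 and 0.86.
- *Group-by-time term of a repeated-measures model.* Simulation used three arms, one arm shifted by 30 at both follow-ups, compound symmetry and 3,000 runs. Power is 0.64, 0.87 and 0.97 at r = 0.5, 0.7 and 0.8, against 0.61 for a one-way ANOVA on the 8-week score. The corresponding main-effect power is 0.44, 0.37 and 0.37.

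**Chance imbalance.** The standard error of a baseline TMT difference between two arms is 53 × √(2/30) = 13.7 points, a 95% range of about ±27 against an assumed effect of 30. A comparison of raw follow-up scores carries r times the observed gap. For a one-standard-error gap this is 0.5 × 13.7 = 6.8 points at r = 0.5 and 0.86 × 13.7 = 11.8 points at r = 0.86.

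**The case against.** The strongest reply is that the text does not shut baseline out. Three groups by three repeated visits is ordinarily read as a mixed ANOVA, whose group-by-time term compares change from a participant's own baseline across arms and performs well when r is high. The unpaired t-test may also be meant for change scores, since Sample Size expresses its effects as mean changes. Both points stand. A reader might infer that neither planned test uses baseline; the documents do not support that, because the ANOVA contrast and the t-test variable are both open.

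A reader might also infer that most of the precision is thrown away. Removing more than half the variance needs r² > 0.5, that is r above about 0.71. The article supports such values only for the WAIS-IV tasks, and in a standardisation sample. Pairing them with the TMT effect is illustrative.

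Nor are the planned tests invalid. Under randomisation an unadjusted comparison is unbiased, and its standard error already allows for chance imbalance.

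Finally, this is a condensed article for a feasibility study, and the choice of contrast or covariates may sit in an analysis plan not shown. Silence on those details is not the point. The article does choose the pairwise between-arm test, and that test has no baseline term as written. The group-by-time test does not remove the difficulty: it is an omnibus test that does not say which arms differ at which visit, and the named follow-on step is the unpaired t-test.

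**Conclusion.** The point holds as a readily available improvement. The plan fixes no baseline-adjusted between-arm comparison, and a better one is available on every reading of the text.

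The size of the gain depends on the reading and on r:

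- If the t-test is applied to follow-up scores, power is about 58%. ANCOVA gives about 70% at an assumed r of 0.5, and 93% to 99% if the WAIS-IV values applied.
- If it is applied to change scores, the loss against ANCOVA is only 7% to 11% of variance at those high values. At r = 0.5 change scores do no better than unadjusted scores, and below that they do worse.
- If the ANOVA is judged on its group main effect, a constant follow-up effect is diluted to two thirds.

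Apart from one degree of freedom, ANCOVA is at least as precise as either t-test at any r. The figures assume 30 per arm, two-sided 0.05, equal SDs, no dropout, and that 30 with SD 53 describes a between-arm difference. The article's own n reproduces only as a within-group calculation, so that last assumption is uncertain. The feasibility criteria are unaffected.

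**What to change.** In the Analysis Plan, replace the unpaired t-tests and the unspecified ANOVA contrast. For each scale, compare arms at 8 weeks and at 3 months with that scale's baseline score as a covariate. Either of these will do:

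- ANCOVA at each visit; or
- one repeated-measures model with the two follow-up scores as responses and terms for arm by visit and baseline by visit.

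Use baseline only as a covariate, not as a level of the time factor. Keep unadjusted means by arm and visit as description.

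The cost is a few sentences of plan wording, a few lines of SAS code and one degree of freedom per comparison. No new data or participants are needed.
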